
Study aim

To evaluate the implementation, effectiveness and cost effectiveness of BI delivered by an alcohol health worker aimed at reducing excessive drinking in routine AED care compared to brief advice and a patient information leaflet (PIL) in hazardous and harmful drinkers identified by universal or targeted screening.

Study objectives

- To conduct a pragmatic multicentre cluster randomised controlled trial of screening and brief interventions for hazardous and harmful drinkers in AEDs in three English regions.
- To compare the effectiveness and cost effectiveness of brief advice conducted by AED staff (including dedicated AHWs) (Tier 1) with referral to an alcohol health worker (Tier 2) of patients with hazardous and harmful alcohol consumption identified by targeted opportunistic or universal screening.
- To assess the relative impact of the three implementation strategies on alcohol screening and brief intervention activity in AEDs.
- To identify the attitudinal, practical, skill, resource, and reinforcing factors that predict successful implementation of screening and brief intervention in AEDs.
- To identify the optimal method of alcohol screening in AED.
- To assess the relative impact of the three implementation strategies on uptake of alcohol services, including an alcohol helpline.

Hypotheses

- Brief Lifestyle Counselling intervention by an alcohol health worker for hazardous and harmful drinkers identified by targeted screening is more effective and cost effective than Brief Advice conducted by AED staff (including dedicated AHWs) in the typical AED setting.
- Brief Lifestyle Counselling intervention by and alcohol health worker and Brief Advice by AED staff (including dedicated AHWs) are more effective and cost effective than an information leaflet alone.
- Access to referral to an alcohol health worker results in greater screening and intervention activity than training of AED staff in screening and brief intervention alone.
- Attitudinal, practical, skill, resource, and reinforcing factors predict screening and intervention activity.
- Briefer screening methods result in greater implementation of screening activity than more complex methods.

Setting

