Nine AEDs in three English regions (North East, London, South East) will be recruited to take part in the study. Recruitment will take place with the assistance of the British Association of Accident and Emergency Medicine (BAEM, of which [name] is a Professor of Accident and Emergency Medicine and adviser to BAEM on the management of alcohol misuse). All AEDs in the three regions that do not have current routine alcohol screening and brief intervention facilities will be eligible to participate. AEDs will be selected to provide a range of both urban and rural catchment areas.

Design

AEDs will be randomly allocated to one of three implementation conditions (leaflet, brief advice or brief lifestyle counseling intervention) in a cluster randomized design such that there will be 3 AEDs in each condition. AEDs will be randomized to one of three screening conditions (described below) such that there will be 3 AEDs in each condition (see Table **1**). Patients enrolled in the study will have a baseline research assessment carried out by structured interview, and followed in parallel groups over 6, and 12 months. Outcome assessment will be by face to face or telephone interview conducted by a researcher.

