In both intervention conditions the research team and specialist clinicians will train and support all participating AEDs in implementing screening systems tailored to the operational model of the AED. Where possible computerized screening tools will be developed to be embedded in AED computerized records systems.

In order to test the relative effectiveness of different screening methods in identifying hazardous and harmful drinkers we intend to conduct a cluster randomized comparison of the modified Paddington Alcohol Test (PAT) (adapted from Patton et al, 2004), the FAST Alcohol Screening Test (FAST; Hodgson et al., 2002) and the modified single item screening test, Single Alcohol Screening Question (SASQ) (adapted from Canagasaby & Vinson, 2005): “How often do you have X or more standard drinks on one occasion?”, where X = 6 for women and 8 for men, with monthly, or weekly, or daily or almost daily considered a positive screen (1 drink = unit of alcohol). The original SASQ has been adapted to the UK’s standard drinks and validated during our pilot research. The new question has a higher sensitivity and specificity then the original SASQ when compare to the gold standard Alcohol Use Disorders Identification Test (AUDIT).

FAST has undergone validity testing in AED settings as a universal screening tool and has been found to be of high sensitivity and specificity (Hodgson et al., 2002) and performs well in comparison to the currently recognised ‘gold standard’ the Alcohol Use Disorders Identification Test or AUDIT.

PAT has been simplified to fit more with the pragmatic nature of this trial by focussing on two questions that have emerged in previous studies (Patton et al., 2004) with high sensitivity and specificity whilst also retaining it’s targeted screening feature.

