However, it is unclear which approach is most effective in identifying cases in the typical AED setting. The modified PAT (SIPS-PAT) is a targeted screening tool which is applied in cases with presenting conditions commonly associated with alcohol misuse. The original PAT has been used at St Mary’s Hospital embedded in the standard clinical assessment process. SASQ on the other hand has been studied in PHC and, based on our pilot research, is more likely to be adopted by busy AED staff. The FAST has been used mainly in a research screening context to establish prevalence rather than as a clinical tool. Also this single question in the modified SASQ will identify individuals whose level of drinking is more likely to lead to AED attendance, and is the same first item of the FAST questionnaire, which was found to identify 50% of hazardous and harmful drinkers (Hodgson et al., 2002).

Brief intervention implementation conditions

1. *Control condition:* AED staff (including dedicated AHWs) in the control condition will be trained to apply the appropriate screening method and record the screening outcome, will feedback the result of screening to patients and offer them a patient information leaflet (PIL. The PIL from the Drink-Less Programme and has been extensively pre-tested with clinicians and patients in PHC and will be used in this trial. The PIL will also contain a number for Drinkline where the patient can access further information). The PIL to be used in this trial will be ‘Alcohol and Sensible Drinking’ as in the PHC study.

2. *Brief Advice condition:* AED staff (including dedicated AHWs)will be trained to carry out screening and deliver up to 5 minutes of simple structured brief advice for hazardous and harmful drinkers presenting to the AED, using the Drink-Less brief intervention materials (level 1) as in the PHC study. Patients in this condition will also receive a Patient Information Leaflet (PIL) as above, including a number for Drinkline.

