In the Brief Lifestyle Counselling condition the training and support for AED staff will be the same as in the simple structured advice condition except that staff will be trained to screen and refer to the AHW. The equivalent of approximately 0.5 WTE AHW salary per AED has been allocated. In some areas it may be more practical to have one AHW split between two AEDs. In other areas different configurations can apply. The AHW will be responsible for training and supporting the AED staff in implementing screening and referral over the course of the project. The AED staff will also be supported in implementation of the screening and research procedures by a member of the research team.

Inclusion criteria

AEDs: Eligible AEDs will be those not already providing routine screening and SBI.

Patients: Any AED patients scoring positive on the modified PAT, FAST or modified SASQ aged 18 or over, and who are alert and orientated, resident within 20 miles and able to speak, read and write English sufficiently well to complete study questionnaires.

Exclusion criteria

Those who are currently seeking help for alcohol problems and those who are involved in any alcohol research study will be excluded. Any patients within the AED setting who are severely injured, suffering with a serious mental health problem and/or who are grossly intoxicated will also be excluded from the study. Finally patients with no fixed abode will be excluded from the study.

Consent

Consent to participate will be obtained in a 2 stage process. AED staff (including dedicated AHWs) will initially establish verbal consent to be check eligibility to take part, collect some basic demographic information and to be screened. Those who then are positive on FAST or modified SASQ or SIPS-PAT as applicable, will have the study explained to them verbally by AED staff (including dedicated AHWs) and in writing (using the patient information sheet). Written informed consent will be obtained by AED staff (including dedicated AHWs). This will include permission to give the patient's data and contact details to the research staff, and provide the research team with access to the patients AED records, and to participate in follow up after 6, and 12 months. The research team will then contact the patient within two weeks to thank him/her to take part in the study.

Measures

Staff attitudinal and organisational measures:

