The research team will identify the total number of patients over 18 attending each AED during the recruitment period, the total number of patients screened, the number screening positive, and the number receiving an alcohol intervention (either a leaflet or brief advice by AED staff (including dedicated AHWs)or brief lifestyle counselling intervention by the AHW) according to the method described by Babor et al. (2005). This will allow calculation of the overall screening rate, the screen conversion rate (proportion of positive screens), and the intervention rate in the different settings. We will also compare these measures between AEDs assigned to the SIPS-PAT versus the modified SASQ versus FAST screening methods.

Reattendence to AEDs over the 6, and 12 month follow up period of patients participating in the study will be assessed using computerised admission records and compared with admissions by the participating group of patients in the 6 month before entry into the study. The sustainability of the screening and intervention approaches will be assessed by examining the extent to which screening and intervention activity continues after the end of the formal study recruitment period.

Patient measures:

*Baseline*

Before receiving the initial PIL and/or brief advice intervention and/or brief lifestyle counselling intervention, participants will be invited by AED staff (including dedicated AHWs) to provide the contact details and complete the Extended AUDIT, EQ5D, Short-SUQ and modified Readiness to change Ruler. Participants in the extended intervention will complete the AUDIT at the same stage as those in other groups.

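### The screening comparison cannot estimate sensitivity, specificity or missed cases, and raw positive-screen rates from three AEDs per tool are too weak to name an optimal method

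*Protocol*

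**What the plan says.** - **Aim.** Study objectives: "To identify the optimal method of alcohol screening in AED". Screening conditions: "In order to test the relative effectiveness of different screening methods in identifying hazardous and harmful drinkers we intend to conduct a cluster randomized comparison"; all three tools are included.
- **Allocation.** Design: "AEDs will be randomized to one of three screening conditions (described below) such that there will be 3 AEDs in each condition". Each AED applies one tool. SIPS-PAT is used on targeted presentations; FAST and M-SASQ are used universally.
- **Who enters.** Inclusion criteria: "Any AED patients scoring positive on the modified PAT, FAST or modified SASQ aged 18 or over". Consent: "Those who then are positive on FAST or modified SASQ or SIPS-PAT as applicable, will have the study explained to them".
- **Who completes the AUDIT.** Under Patient measures (Baseline), "participants will be invited by AED staff (including dedicated AHWs) to provide the contact details and complete the Extended AUDIT". The purpose given is to establish severity and to check that the intervention groups match at baseline.
- **What is compared.** System measures plans the screening rate, the conversion rate (the share of screens that are positive) and the intervention rate, compared between AEDs by tool.
- **Overlap of two tools.** Screening conditions says the M-SASQ question "is the same first item of the FAST questionnaire, which was found to identify 50% of hazardous and harmful drinkers".

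**The concern.** The stated question concerns case detection, but the data can answer it only in part. No screen-negative patient receives a reference assessment and no patient is described as classified by two tools. The conversion rate rises when a tool finds more true cases, when it labels more non-cases positive, or when its three AEDs serve heavier-drinking catchments. For SIPS-PAT it also reflects the targeting. A tool could be reported as optimal for any of these reasons.

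The sample size section says that powering for the intervention outcome also covers screening method, but gives no calculation for that comparison.

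A within-patient comparison of two tools is within reach, because one tool's question is said to sit inside the other. The protocol neither describes that comparison nor says that item-level answers are kept.

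**Working it through.** **1. The protocol's own figure.** There is none for the tool comparison. The base sample size (5% v 18%, two-sided 5%, 80% power) is 109 per group. The usual two-proportion formula gives 94, or 109 with continuity correction, so it reproduces. It concerns drinking at 6 months and says nothing about precision for screening rates.

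**2. What screen-positives alone can show.** Sensitivity = positive rate × PPV ÷ prevalence. With no AUDIT in screen-negatives, prevalence is unknown. Assumed values:

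| Tool | Positive | PPV | True positives per screen | Sensitivity, prevalence 30% | Sensitivity, prevalence 40% |
|---|---|---|---|---|---|
| A | 30% | 85% | 0.255 | 0.85 | 0.64 |
| B | 25% | 90% | 0.225 | 0.75 | 0.56 |

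At equal prevalence A ranks first. If A's AEDs have 40% and B's have 30%, the ranking reverses (0.64 v 0.75). The same observed data fit either case.

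**3. Precision of the conversion-rate comparison, three AEDs v three.** Inputs: ICC 0.04 (the protocol's figure for the drinking outcome) or 0.01 (assumed); 400 screened per AED and 20–40% positive (assumed).

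- Variance of one AED's rate = p(1−p)[ICC + (1−ICC)/400]; SE of the difference = √(2 × variance/3); multiplier t(0.975, 4 df) = 2.776.
- p = 0.3, ICC 0.04: 0.21 × 0.0424 = 0.00890; SE 0.0771; half-width 0.214.
- p = 0.3, ICC 0.01: 0.21 × 0.012475 = 0.00262; SE 0.0418; half-width 0.116.
- Over p = 0.2 to 0.4: ±19 to 23 points (ICC 0.04) and ±10 to 12 points (ICC 0.01).

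The 400 is on the low side: 131 recruits need 131/0.30 = 437 screened at 30% positive and 131/0.20 = 655 at 20%, even with full consent. This hardly matters. With 5,000 per AED and p = 0.3 the half-widths are still about 21 and 10.5 points, because the number of AEDs sets the limit.

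Power for 30% v 40% (cluster-level t test, 4 df, 300 to 5,000 screened per AED) is 16–17% at ICC 0.04, where 80% power needs a difference of about 30 points. At ICC 0.01–0.02 power is 26–49%, and the detectable difference is 15 to 22.5 points.

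**4. What a paired comparison adds.** With 3 × 400 = 1,200 patients screened in the FAST AEDs and discordant shares b and c, SE = √[(b + c − (b−c)²)/1,200].

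- 15% and 3%: √(0.1656/1,200) = 0.0117; half-width 2.3 points.
- 10% and 5%: √(0.1475/1,200) = 0.0111; half-width 2.2 points.

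These are conditional on three AEDs and ignore variation between them, so they are not like for like with step 3. A related quantity shows the cost of allowing for that variation: the share of 393 FAST-positive recruits who are also M-SASQ positive, assumed 50–90%. Its half-width is about 5 to 3 points ignoring clustering. With design effect 1 + 130 × 0.04 = 6.2 it is 12 to 7 points, or 27 to 16 points using t on 2 df.

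**The case against.** The strongest reply is that this is not an accuracy study. The protocol cites the AUDIT as the standard in earlier validation of FAST and M-SASQ; in this trial the AUDIT measures severity and is kept short so that assessment does not act as intervention. The tools are compared as used in routine care, with a hypothesis that briefer tools are implemented more. The universal arms also record presenting conditions, to support the targeted v universal comparison. This stands as a defence of the uptake comparison. It does not cover the stated test "In order to test the relative effectiveness of different screening methods in identifying hazardous and harmful drinkers", and recording presentations does not reveal missed cases.

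A reader might infer four stronger things, which the documents do not support:

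- **That the trial can show nothing about detection.** Confirmed yield can be compared, and relative accuracy could in principle be estimated if randomisation balanced prevalence. Three AEDs per tool cannot be relied on for that.
- **That M-SASQ misses half of cases.** The 50% comes from a cited source, is attached to the first FAST item, and carries no cut-point. M-SASQ is scored positive at monthly or more often.
- **That collected data are being left unused.** Staff are said to record the screening outcome; item-level recording is not stated, and an analysis plan not shown could contain the paired analysis. But if item 1 is not recorded, no later plan can recover it.
- **That the paired comparison would settle FAST v M-SASQ.** Patients positive on M-SASQ but negative on FAST never receive an AUDIT. Verification could show cases M-SASQ misses but never cases FAST misses, so it would favour FAST.

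**Conclusion.** The point holds in a limited form. As designed, the trial cannot estimate sensitivity, specificity or missed cases for any tool. Its planned detection measure does not distinguish true from false positives and is very imprecise: about ±21 points at ICC 0.04 or ±12 at ICC 0.01, assuming 30% positive and 400 screened per AED. The ICC for screening rates is not given, and 0.04 is borrowed from the drinking outcome. The identification of the problem needs no numerical assumption, since it follows from who receives the AUDIT. The objective of naming an optimal method therefore claims more than the design supports. The improvement is cheap, and it is a protocol matter because it concerns which answers are recorded and what may be concluded. The intervention comparison is not affected.

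**What to change.** 1. **Confirmed yield.** Beside the conversion rate, report by tool the proportion of consenting screen-positives who are hazardous or harmful on the baseline AUDIT, at a cut-point fixed in advance, with consent rates. Report confirmed cases per eligible attender as well as per patient screened, because SIPS-PAT is targeted and the other tools are universal. System measures already counts attenders over 18, the nearest available denominator. Give cluster-level intervals for these between-AED comparisons.
2. **Paired comparison.** In the FAST AEDs, record the item 1 answer for every screened patient, score M-SASQ by the rule in Screening conditions, and report the paired FAST v M-SASQ classification as supporting evidence. Show both discordant cells. State that AUDIT verification exists only for FAST-positives who consent, so it can count cases M-SASQ would miss but not cases FAST misses, and that the result is conditional on three AEDs.
3. **Claim.** State that sensitivity and specificity are not estimated, and limit the optimal-method conclusion to uptake and AUDIT-confirmed yield. Do not use the 50% figure as evidence against M-SASQ.

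**Cost.** Item-level recording of one question already asked, some derived variables, and protocol wording; no extra sites and no added patient assessment. The paired comparison covers only two of the three tools, and the conclusion is narrower. Estimating absolute sensitivity and specificity would need the AUDIT in at least a sample of screen-negatives, which this fix does not include.

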**Research Protocol**

Synopsis

This pragmatic trial with cluster randomization of AEDs is designed to evaluate the effectiveness and cost-effectiveness of screening methods (modified PAT vs FAST vs modified SASQ) and interventions (Leaflet vs Brief advice vs Brief counselling) in routine AED care. Due to the design implications of a multi-level factorial design in AEDs the proposed trial involves a universal screening approach in which relevant data for a sub-sample of linked presentation population is collected. Therefore, the trial design encompasses a 3x3 factorial trial, screening method (modified PAT vs FAST vs modified SASQ) and intervention (Leaflet vs Brief advice vs Brief lifestyle counselling). The main advantages of utilising a factorial approach are twofold. First each of the three elements (screening tool and intervention) can be analysed independently with sufficient power to make meaningful interpretation of relative effectiveness. Second, the method enables meaningful interpretations of the relative effectiveness of any combination of screening method and intervention. Because the universal screening population encompasses a sub-group of linked presentation targeted population we can make meaningful comparisons of the relative effectiveness and interactions associated with screening approach in AEDs. Nine AEDs across the North East, London and the South East Regions of England will be recruited. AEDs will be randomly allocated to one of three intervention conditions: the patient information leaflet control condition (n=3), the structured brief advice condition (n=3); and lifestyle counselling by an Alcohol Health Worker (n=3). To test the relative effectiveness of different screening methods all AEDs will be randomised to either a modified single item screen (Single Alcohol Screening Question; M-SASQ) or a modified Paddington Alcohol Test (SIPS-PAT) or FAST Alcohol Screening Test (FAST) screening method. AEDs in the modified PAT condition will use targeted screening as per the standard PAT protocol. AEDs in the FAST and modified SASQ conditions will use universal screening for case identification and collect information about whether a patient would be part of a linked presentation group and then use statistical simulation to analyse any interactions. Screening randomisation will be stratified by median AED admission rates (2 levels) and intervention condition (3 levels). Each AED will recruit a minimum of 131 patients who are hazardous or harmful drinkers into the trial and a short baseline assessment will be carried out. Outcome will be assessed at 6, and 12 months after intervention. Outcomes will include system implementation outcomes and patient outcomes. We will also examine the practitioner and organisational factors associated with successful implementation.

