The AED study design differs from the PHC study in not having targeted versus universal screening as a separate factor in the design. There are two main reasons for this. First, we have looked closely at the potential of a factorial design including universal versus targeted screening. However, the number of AEDs that would be required to have a separate screening factors (minimum n=18) would exceed the likely number of AEDs agreeing to participate in the there regions (based on previous experience from our national AED survey (Drummond et al., 2003)). Second the PAT has been designed as a targeted screening method in the context of routine AED assessment. The FAST and SASQ on the other hand have been designed as universal screening tools. Therefore we propose that universal versus targeted screening be studied in two ways within this trial. First we will randomize AEDs to targeted screening with the modified PAT and universal screening with FAST or the modified SASQ, which is appropriate to the design of the instruments. Second we will record the patients’ presenting clinical conditions and demographic factors in the universal screening arms of the study to identify which factors are most strongly associated with alcohol positive cases. Together these findings will allow the comparison of targeted and universal screening and lead to the development of clinical guidelines for AEDs on the most efficient form of targeted screening approach.

Table **1**. Overall AED study design.

| Intervention condition **>** | Leaflet by AED staff | Brief advice by AED staff | Brief Lifestyle  Counselling intervention | Totals |
| --- | --- | --- | --- | --- |
| Screening condition V |
| FAST Alcohol Screening Test | AED n=1;  Patients n=131 | AED n=1;  Patients n=131 | AED n=1;  Patients n=131 | AED n=3;  Patients n=393 |
| Modified Single Alcohol Screening Question | AED n=1;  Patients n=131 | AED n=1;  Patients n=131 | AED n=1;  Patients n=131 | AED n=3;  Patients n=393 |
| SIPS Paddington Alcohol Test | AED n=1;  Patients n=131 | AED n=1;  Patients n=131 | AED n=1;  Patients n=131 | AED n=3;  Patients n=393 |
| Total per intervention | AED n=3  Patients n=393 | AED n=3  Patients n=393 | AED n=3  Patients n=393 | AED n=9  Patients n=1179 |

Screening conditions

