3. *Brief Lifestyle condition:* This is based on the St Mary’s Hospital model. AED staff (including dedicated AHWs) will be trained to carry out universal alcohol screening and to refer hazardous and harmful drinkers identified by screening to an Alcohol Health Worker (AHW), by making an appointment usually the following day or as soon as possible after AED attendance. Before leaving the AED the patients in this condition will be given a PIL and Simple structured advice as above. The AHW will be experienced in carrying out alcohol assessment and brief interventions. The AHW will carry out a brief lifestyle counseling intervention lasting for 20 minutes using the modified Drink-Less brief intervention materials (level 2).

AED recruitment

Eligible AEDs in the participating regions will be contacted initially by phone and mail to canvass participation in the study. We will use contacts previously made in our national survey of AEDs (Drummond et al., 2003) and through the BAEM with [name] assistance. Thereafter site visits will be made by the research team to explain the trial protocol, secure clinician consent to participate in the study and to organize training.

Training and support

All participating AEDs will be provided with training and support appropriate to the allocated condition in the study. In the control condition staff will be trained by experienced SBI clinical trainers to carry out screening, feedback and provide a PIL. A member of the research team and a specialist clinician will provide ongoing support in implementing the research and clinical procedures.

In the Brief Advice condition training and support will be provided by a specialist clinician (Alcohol Health Worker) who will act as clinical coordinator for the study, and a member of the research team. Training will be carried out by experienced trainers for medical, nursing and administrative staff in seminars and individual training (see ‘incentives’ below). Trainers will be Alcohol Health workers recruited from local alcohol agencies. Each AED will have an allocated clinical coordinator who will champion screening and brief intervention and provide ongoing support and supervision for AED staff, including an AED staff support group. The research coordinator will provide support on implementation of the research procedures.

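### The counselling condition tells its staff to screen universally, but one of its three AEDs is the SIPS-PAT AED, which the rest of the protocol requires to screen targeted presentations

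*Protocol*

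**What the plan says.** Four parts of the protocol set who is screened in a SIPS-PAT AED.

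- **Synopsis.** "AEDs in the modified PAT condition will use targeted screening as per the standard PAT protocol", whereas "AEDs in the FAST and modified SASQ conditions will use universal screening for case identification".
- **Design.** Targeted versus universal screening is to be studied as a randomised contrast: "First we will randomize AEDs to targeted screening with the modified PAT and universal screening with FAST or the modified SASQ". Table 1 then puts one SIPS-PAT AED in each intervention column, counselling included: "SIPS Paddington Alcohol Test | AED n=1; Patients n=131 | AED n=1; Patients n=131 | AED n=1; Patients n=131".
- **Screening conditions.** The modified PAT "is a targeted screening tool which is applied in cases with presenting conditions commonly associated with alcohol misuse".
- **Brief intervention implementation conditions.** Leaflet staff "will be trained to apply the appropriate screening method and record the screening outcome". Brief advice staff "will be trained to carry out screening and deliver up to 5 minutes of simple structured brief advice". Counselling staff "will be trained to carry out universal alcohol screening and to refer hazardous and harmful drinkers identified by screening to an Alcohol Health Worker". Only the counselling description names a screening approach, and it names the universal one without exception.

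**The concern.** Under Inclusion criteria, a patient enters the trial by screening positive on the instrument used in that AED. Who is screened therefore decides who can be enrolled. If the SIPS-PAT AED in the counselling arm screened all attenders while the SIPS-PAT AEDs in the leaflet and advice arms screened only alcohol-linked presentations, case mix could differ by intervention arm. Screening approach would then be partly confounded with intervention in the primary comparison.

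The screening comparison would also lose one of its three targeted AEDs. With one AED per cell, no second site could replace it. Hypothesis 1, on counselling versus advice after targeted screening, would lose its only directly randomised counselling site.

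**Working it through.** No power formula is needed. The check is a count of cells under each of the two rules.

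**Inputs (Table 1):** 9 AEDs in a 3 x 3 layout, one AED and 131 patients per cell.

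**Reproducing the table:** 3 x 131 = 393 per intervention and 9 x 131 = 1179 in total. Both agree with the protocol.

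**Rule A: screening follows the screening allocation (Synopsis, Design, Screening conditions).**

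| Arm | Targeted AEDs | Universal AEDs | Patients from targeted screening |
|---|---|---|---|
| Leaflet | 1 | 2 | 131/393 = 33.3% |
| Brief advice | 1 | 2 | 131/393 = 33.3% |
| Counselling | 1 | 2 | 131/393 = 33.3% |
| Trial | 3 (3 x 131 = 393 patients) | 6 (6 x 131 = 786 patients) | 393/1179 = 33.3% |

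**Rule B: the counselling description is followed literally.**

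| Arm | Targeted AEDs | Universal AEDs | Patients from targeted screening |
|---|---|---|---|
| Leaflet | 1 | 2 | 131/393 = 33.3% |
| Brief advice | 1 | 2 | 131/393 = 33.3% |
| Counselling | 0 | 3 | 0/393 = 0% |
| Trial | 2 (2 x 131 = 262 patients) | 7 (7 x 131 = 917 patients) | 262/1179 = 22.2% |

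The rules differ in one cell, SIPS-PAT by counselling: 1 AED and 131 patients, a third of the counselling arm. Under Rule A the arms are balanced on screening approach by design. Under Rule B they are not, and the targeted-by-counselling cell is empty.

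**What cannot be calculated.** The protocol gives no figure for how drinkers found by targeted and by universal screening differ in severity or in the primary outcome. The 33.3% is therefore the share of the arm exposed to the ambiguity. It is not an estimate of bias.

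**The case against.** The strongest reply is that the intended rule is clear and that one adjective stands against it. Much of this is right.

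- The Study aim has worker-delivered intervention for drinkers found by either screening approach, so counselling was meant to span both.
- The Consent section applies whichever of the three instruments is relevant to the site.
- The Training and support section promises training that suits the allocated condition. It describes counselling training as matching the advice condition, apart from screening and onward referral. It does not mention universal screening.

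A reader might infer that SIPS-PAT counselling staff will in fact be trained to screen everyone. The protocol does not establish that. It contains one sentence saying so and several pointing the other way.

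A reader might also infer that the intervention arms are already confounded with screening approach. They are not: the imbalance arises only if that one AED follows the counselling description over its own screening allocation. The planned adjustment for known prognostic factors would reduce measured case-mix differences, though not unmeasured ones.

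A third tempting inference is that hypothesis 1 would have no counselling AED at all. That is not supported. The Synopsis has the FAST and modified SASQ AEDs record whether each patient belongs to a linked-presentation group, and both the Synopsis and Planned analysis foresee simulation across the two screening approaches. Even on the literal reading, the FAST and modified SASQ counselling AEDs would supply linked-presentation patients. What would be lost is the directly randomised cell. The replacement would be subgroups identified with other instruments.

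What survives is narrower: the two instructions for one AED cannot both be followed, and no sentence says which prevails.

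**Conclusion.** The contradiction is real and stands in operative text, since the counselling description states what staff are to be trained to do. It affects 1 of 9 AEDs and 131 of 393 counselling patients.

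The consequences depend on the literal reading being acted on. In that case the counselling arm has 0 of 393 patients from targeted screening against 131 of 393 in each other arm, and the screening contrast becomes 2 v 7 AEDs instead of 3 v 6. The counselling side of hypothesis 1 would then rest on linked-presentation subgroups of the FAST and modified SASQ AEDs. If the Synopsis and Design sections govern, the arms are balanced and no harm follows.

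These counts assume that every cell recruits the 131 patients in Table 1. The direction and size of any bias cannot be derived from the protocol. The layout of Table 1 is sound; the fault is one phrase that contradicts it.

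**What to change.** In the description of the Brief Lifestyle condition, replace the reference to universal screening with: *the screening method allocated to the AED (universal in FAST and M-SASQ AEDs, targeted in the SIPS-PAT AED)*. Use the same wording for the leaflet and brief advice conditions and in the training material, so that the intervention descriptions no longer set the screening approach independently.

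An edit to the Synopsis sentence that describes the trial as taking a universal screening approach is optional, because the Synopsis later states which AEDs screen universally and which are targeted.

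The cost is a wording change in the protocol and training material, best made before staff are trained. It needs no additional patients, sites or procedures, and it restores the allocation that the protocol itself sets out.
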